## Abstract

**Introduction:**

Randomised controlled trials (RCTs) in surgery are frequently criticised because surgeon expertise and standards of surgery are not considered or accounted for during study design. This is particularly true in pragmatic trials (which typically involve multiple centres and surgeons and are based in ‘real world’ settings), compared with explanatory trials (which are smaller and more tightly controlled).

**Objective:**

This protocol describes a process to develop and test quality assurance (QA) measures for use within a predominantly pragmatic surgical RCT comparing minimally invasive and open techniques for oesophageal cancer (the NIHR ROMIO study). It builds on methods initiated in the ROMIO pilot RCT.

**Methods and analysis:**

We have identified three distinct types of QA measure: (i) entry criteria for surgeons, through assessment of operative videos, (ii) standardisation of operative techniques (by establishing minimum key procedural phases) and (iii) monitoring of surgeons during the trial, using intraoperative photography to document key procedural phases and standardising the pathological assessment of specimens. The QA measures will be adapted from the pilot study and tested iteratively, and the video and photo assessment tools will be tested for reliability and validity.

**Ethics and dissemination:**

Ethics approval was obtained (NRES Committee South West—Frenchay, 25 April 2016, ref: 16/SW/0098). Results of the QA development study will be submitted for publication in a peer-reviewed journal.

**Trial registration number:**

ISRCTN59036820, ISRCTN10386621.

Strengths and limitations of this studyThis protocol describes the process of developing quality assurance (QA) measures to use within pragmatic surgical randomised controlled trials, which is an area lacking in methodological guidance.Further work will establish if these QA approaches can be used more widely in different contexts.This study will explore the feasibility of obtaining digital videos of open surgery during this study; however, it may not be possible to achieve this with good enough quality or without interfering with the process of surgery. The increasing availability and use of digital imaging and information technologies should facilitate the use of these methods.QA processes require investment of resource and expertise: future work to streamline them is therefore needed.While the addition of QA processes can reduce bias and improve internal validity, they may initially appear to compromise a trial’s generalisability. Provided pragmatic standards are set and monitored, this should be avoided.

## Introduction and rationale

Randomised controlled trials (RCTs) in surgery are notoriously difficult to design and conduct, due to numerous methodological and cultural challenges. Many of these challenges relate to the fact that surgical procedures are complex healthcare interventions, meaning that ‘unlike 20 milligram tablets, no two procedures are the same’ and achieving standardisation of surgical techniques and processes is difficult.^1^ This is partly because surgeons naturally undertake procedures in (slightly) different ways and have differing skill levels, which may influence rates of postoperative complications and reoperation.^2^ A lack of consideration for intervention standardisation and surgeon expertise in the context of RCTs may introduce bias, compromising internal validity. This is acknowledged in guidance such as Consolidated Standards of Reporting Trials of Non-Pharmacologic Treatment (CONSORT-NPT) and Standard Protocol Items: Recommendations for Interventional Trials (SPIRIT), which provides a checklist of 33 items to be reported in trial protocols. They recommend reporting precise details of the intervention and its components to enable replication in routine practice, information about standardisation, procedures for monitoring adherence to intervention protocols and consideration for the expertise of care providers.

Neither CONSORT-NPT nor SPIRIT differentiate between the information required in pragmatic or explanatory settings. This may be because it is rare for trials to be purely pragmatic or explanatory: trial design is not dichotomous and there is a continuum between the two extremes. In explanatory trials, which determine the efficacy of interventions, great detail may be necessary because the interventions are often novel and their safety needs to be assessed within carefully controlled settings. Pragmatic trials, which determine whether interventions are effective in the real world, are often multicentre studies with large numbers of surgeons.^3^ Under such circumstances, specifying each operative step is likely to create difficulties, and ensuring that each step was delivered as planned may be unrealistic. A balance between adequate standardisation and practicality is therefore necessary and appropriate. One way of achieving this is to determine the minimum active ingredients of the intervention—those that are thought to optimise outcomes or those that are different between the interventions in each trial group—and the degree to which they need to be standardised. In this way, monitoring only the key components may be sufficient, rather than monitoring all components and steps, in order to ensure the intervention is actually delivered as planned.^4^ This approach would also account for the fact that most trials sit within the pragmatic-explanatory continuum rather than being one or the other.

It is, therefore, important to provide reassurance about the standards of surgery in all RCTs, while recognising that this may vary according to trial design. One way of achieving this is to undertake quality assurance (QA), defined as the process(es) of ‘directing the performance and behaviours of practitioners and institutions toward more appropriate and acceptable health outcomes’.^5^ Undertaking QA in surgery has been summarised in a systematic review of laparoscopic colorectal surgical studies.^6^ The review identified three distinct categories of QA measures: (i) trial entry criteria for surgeons and centres, (ii) standardisation of surgical techniques and (iii) monitoring of surgeons and/or units. Despite this, the use of such QA measures is rarely reported. In addition, it did not consider how QA processes may differ between pragmatic and explanatory trials. A recent systematic review of 80 RCTs found that 18% used entry criteria for surgeons or centres, 29% attempted to standardise the surgical procedures under evaluation (although most did not describe what the standards were), and 28% undertook some form of monitoring during the trial.^7^ An additional problem is that the QA processes were often selected arbitrarily and relied on surgeons’ self-reported data, rather than objective measurements, which leaves them open to criticism. Practical, robust approaches to QA in pragmatic surgical studies are lacking. The aim of this study, therefore, was to develop and test QA processes for pragmatic surgical trials, in the context of a predominantly pragmatic RCT evaluating surgical techniques in upper gastrointestinal cancer surgery (Randomised Oesophagectomy–Minimally Invasive or Open (ROMIO), HTA 14/140/78).^8 9^

### The ROMIO study

The purpose of the ROMIO study is to compare, in patients with cancer of the oesophagus and oesophagogastric junction, the clinical and cost effectiveness of laparoscopically assisted (LAO) and open (OO) surgical procedures in terms of recovery, health-related quality of life, cost and survival. The RCT will be conducted in at least eight UK centres. The ROMIO study is predominantly pragmatic, as demonstrated by the Pragmatic-Explanatory Continuum Indicator Summary II wheel provided in figure 1.^10^ For example, it is multicentre and involves more than 40 surgeons. It has broad inclusion criteria and it is expected that at least 60% of patients undergoing oesophagectomy will be eligible to participate. The primary outcome is patient centred and secondary outcomes include resource use and other clinical and patient-reported outcomes. Despite this, however, assessing QA is crucial, to ensure that the LAO is performed to a similar standard as the OO, enabling a fair comparison to be made between the two techniques. Within the ROMIO pilot study, work was undertaken to begin the process of establishing QA methods. This protocol outlines plans to test and assess the feasibility of implementing these QA methods for the purposes of a multicentre RCT in surgery.

**Figure 1 F1:**
[figure not shown]
Pragmatic-Explanatory Continuum Indicator Summary II wheel: a visual representation of the predominantly pragmatic nature of the Randomised Oesophagectomy–Minimally Invasive or Open study.^10^ Trials that take an explanatory approach produce wheels nearer the hub; those with a pragmatic approach are closer to the rim.

## Objectives

To examine the variability of performance of oesophagectomy and agree on standardisation of surgery that are acceptable for a predominantly pragmatic multicentre trial.To pilot a tool to assess the quality of oesophagectomy undertaken within the ROMIO study.To pilot a tool to enable ongoing monitoring of surgeons’ technical performance throughout the RCT.To explore the feasibility of using intraoperative digital photography and videos as methods for assessing QA in an RCT.To develop a feedback system for surgeons participating in the trial.

## Methods and analysis

Methods to assess QA will be developed from work initiated in the pilot RCT. There are three categories: (i) entry criteria for surgeons and centres, (ii) standardisation of surgical techniques and (iii) monitoring of surgeons and centres during the trial. Methods to assess QA in each of these categories will carefully consider the balance between extensive selection (of centres and surgeons) and standardisation (of technique) with the predominantly pragmatic nature of the study.

## Entry criteria for centres

The criteria used to select centres to participate in the ROMIO study will be based on discussions within the study management group, informed by: recommendations for cancer centres (>50 cases per year), experience of team working in trials (agreement of at least two surgeons to enter patients into the trial) and commitment (shown by the provision of centre-level data for submission to the National Oesophago-Gastric Audit).

## Entry criteria for surgeons

Rather than prevent surgeons from participating in the study, the purpose of this aspect of QA was predominantly to enable (i) variations in surgical technique and skill to be described, facilitating contextualisation of the results, (ii) provision of feedback and (iii) to establish whether LAO was broadly being performed to the same standard as OO. The feasibility of collecting videos of the abdominal phase of OO will be established. If found to be possible, participating surgeons will be required to submit one unedited video of the abdominal phase of OO (the ‘standard’ technique), in line with existing literature.^2^ Because LAO represents a ‘new’ technique, and to prevent surgeons from selecting only their ‘best’ example, two unedited videos of the abdominal phase of LAO will be required. All videos will be pseudonymised.

A schema outlining the proposed development and validation of the video assessment tool is provided in figure 2. Current available methods for assessing the quality of surgeons’ technical skills from videos include hierarchical task analysis^9^ and the Objective Structured Assessment of Technical Skills (OSATS) tool.^11^ OSATS is suitable for use with any type of surgical procedure (although has not been formally tested in the context of oesophagectomy) whereas hierarchical task analyses are developed individually for specific procedures. A hierarchical task analysis for oesophagectomy (HTA-O) was developed during the pilot phase of the ROMIO study^9^; however, it has not yet been formally tested. Both OSATS and HTA-O measures will be piloted simultaneously using ‘think aloud’ techniques, whereby a researcher will observe a surgeon (from the review team, see the ‘Data analysis’ section below) while reviewing an operative video.^12^ The surgeon will be asked to complete each measure and express their thoughts while doing so, and to vocalise any general feelings about the technical skills displayed on the video. The ‘think aloud’ sessions will be audio recorded, transcribed verbatim and analysed thematically. Based on the findings from this process, the existing measures (OSATS and HTA-O) may be amended or combined, and new domains added. The ‘think aloud’ process will be iterative—that is, it will be repeated with different videos until the surgeon has no further comments—and stop once the study team are satisfied that no new amendments are necessary. It is anticipated that two surgeons will be involved in this piloting phase.

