## Data collection

Patients will be asked to give written informed consent for video and photographic recordings of the procedure (separate to consent for recruitment into the ROMIO study itself), and transfer of the data to the trial coordinating centre (using local and study consent forms). LAO videos will be collected directly from the laparoscopy ’stack' already in routine use for the operations. Video recording will start from when the surgeon inserts the camera port and will end when the camera is removed after the procedure. Processes for obtaining videos of OO will be established as part of this study. Photographs will be taken using the laparoscopy ‘stack’ (for LAO and OO) and collected for each of the key phases identified during the ‘standardisation of surgical procedures’ process (described above).

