### Feasibility data

An additional objective of this study is to collect information about the feasibility of developing QA processes involving the collection of digital images. Technical issues (and their solutions, if appropriate) will be documented as they arise and ‘standard operating procedure’ documents will be produced for both the video and photography QA aspects of this study. We envisage that it may be particularly problematic to collect digital videos of open surgery, that sufficiently match the quality of laparoscopic procedures. Specific attention will be paid to developing solutions to overcome the barriers to collecting such data, including the need to minimise any interference with the usual process of surgery.

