### Video assessments (surgeon entry criteria)

Where videos are incomplete (eg, a component of the operation has not been captured), the surgeon will be asked to provide a further video. Videos of surgeons receiving a summary judgement of ‘poor’ skill (or worse) will automatically be discussed and reviewed by the study team.

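### Two surgeon-chosen LAO videos lessen best-case selection but do not prevent it, and the comparison of LAO with OO standards is not like for like

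*Protocol article*

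**What the plan says.** All of this is in the Protocol article. Under Entry criteria for surgeons, one of three purposes of the entry videos is "to establish whether LAO was broadly being performed to the same standard as OO". The samples differ by technique. For OO, "participating surgeons will be required to submit one unedited video of the abdominal phase of OO", and only if recording turns out to be possible: "The feasibility of collecting videos of the abdominal phase of OO will be established". For LAO the number is two, for two stated reasons. LAO is the newer technique, and the second video is meant "to prevent surgeons from selecting only their ‘best’ example, two unedited videos of the abdominal phase of LAO will be required".

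Under Video assessments, "Where videos are incomplete (eg, a component of the operation has not been captured), the surgeon will be asked to provide a further video". A summary judgement of poor skill or worse leads to review by the study team. No rule is given for combining a surgeon's two LAO ratings.

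Under Data collection, LAO recordings come from equipment "already in routine use for the operations". Under Feasibility data, the authors write: "We envisage that it may be particularly problematic to collect digital videos of open surgery".

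**The concern.** The article names a threat, that surgeons will submit flattering cases, and offers a number of videos as the protection. A number does not control which cases are sent. Requiring unedited footage stops cutting within a recording, but not choosing between recordings. No section says that cases are consecutive, randomly drawn, limited to a date window or picked by the trial team. A surgeon with several recordings can send the best two.

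The protection, such as it is, applies to LAO only. The article calls quality assurance crucial to a fair comparison of the techniques (The ROMIO study), yet the two sets of videos that inform this judgement are collected under different rules. A difference in ratings, or the absence of one, could then reflect how cases were chosen and not how well the operations were done.

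**Working it through.** The article gives no numerical target for the video assessment, so there is no figure of its own to reproduce. The check is an illustration on stated assumptions.

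**Inputs from the article.** One OO and two LAO videos per surgeon; no case-selection rule; no rule for combining the two LAO scores.

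**Assumptions, not in the article.** The surgeon chooses the best of m recorded cases in each technique, with m from 2 to 50. True skill is equal in the two techniques. Scores of one surgeon's cases are independent and normal with SD 1, so results are in case-to-case SD units and 0 is the typical case.

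**Formula.** The expected r-th smallest of m standard normal scores is E(r,m) = ∫ x · m·C(m−1, r−1) · Φ(x)^(r−1) · [1−Φ(x)]^(m−r) · φ(x) dx. The best case is b = E(m,m) and the second best is s = E(m−1,m). OO is scored at b. LAO, if the two scores are averaged, is scored at (b+s)/2, so LAO minus OO is (s−b)/2.

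**Step 1: equal pools, LAO scores averaged.**

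| m | Best, b | Second best, s | Mean of best two | LAO − OO |
|---|---|---|---|---|
| 2 | 0.564 | −0.564 | 0.000 | −0.564 |
| 3 | 0.846 | 0.000 | 0.423 | −0.423 |
| 5 | 1.163 | 0.495 | 0.829 | −0.334 |
| 10 | 1.539 | 1.001 | 1.270 | −0.269 |
| 20 | 1.867 | 1.408 | 1.638 | −0.230 |
| 50 | 2.249 | 1.855 | 2.052 | −0.197 |

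A simulation at m = 10 gave 1.539 and 1.270, which agrees.

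The fourth column tests the claim of prevention. The two LAO videos still overstate the typical case by 0.83 to 1.64 SD for pools of 5 to 20. The overstatement vanishes only when exactly two recordings exist. The second video does dampen selection, for example from 1.163 to 0.829 at m = 5.

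**Step 2: unequal pools, LAO scores averaged.** The difference is the mean of the best two LAO cases minus the best OO case.

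- OO 1, LAO 5: 0.829 − 0 = +0.83
- OO 1, LAO 10: 1.270 − 0 = +1.27
- OO 3, LAO 10: 1.270 − 0.846 = +0.42
- OO 5, LAO 10: 1.270 − 1.163 = +0.11
- OO 3, LAO 5: 0.829 − 0.846 = −0.02
- OO 10, LAO 5: 0.829 − 1.539 = −0.71

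An OO pool of about half the LAO pool is enough to cancel or reverse the sign.

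**Step 3: other ways to combine the LAO scores, equal pools.** If the better LAO video counts, the difference is b − b = 0. If the worse one counts, it is s − b, for example 0.495 − 1.163 = −0.668 at m = 5.

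**Step 4: no selection.** With consecutive or randomly drawn cases, every video has expectation 0. The expected difference is 0 even with one OO and two LAO videos. Only precision differs: variance 1 against 0.5 per surgeon for independent cases.

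**Step 5: counting poor judgements.** If any poor video triggers review, a surgeon with two videos has probability 1−(1−p)² against p with one. At an assumed p of 5% per video this is 1 − 0.95² = 9.75% against 5.0%. With a within-surgeon correlation of 0.8 the LAO figure falls to 7.5%. The rate is assumed; the point is only that a count per surgeon is not comparable between techniques and a count per video is.

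**The case against.** Several points on the other side have force.

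- Read literally, the sentence concerns submission of a single best case alone, and asking for two does stop that. The newness of LAO is a separate and deliberate reason for looking at it twice. Both points stand. Neither supplies a safeguard for OO or makes the two samples comparable.
- The article does not say outright that surgeons choose the cases. That is inferred. The plan's own worry about surgeons selecting presupposes it, and no section provides otherwise.
- The stakes are limited. The videos are not meant to keep surgeons out of the trial, the comparison is described as broad, with no test or margin, and OO videos may not be collected at all. Other monitoring does not rest on a chosen entry case: photographs are encouraged for every recruited patient, and specimens are assessed uniformly by blinded pathologists. This lowers the severity but leaves the sampling flaw in place.
- Standard operating procedures for video are planned and the article condenses a fuller protocol, so a selection rule could sit there. But the article does state a mechanism and its purpose, and that mechanism does not achieve the purpose.

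A reader might also infer that replacing incomplete videos gives surgeons a second chance to choose. The trigger is incomplete capture, not poor performance, so this is conjecture. Nor does one OO video per surgeon defeat the first objective: the article promises to describe variation, not to separate surgeon from case variance.

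**Conclusion.** The point holds as a modest design flaw with a cheap remedy. Two surgeon-chosen LAO videos lessen best-case selection but do not prevent it, the one OO video has no safeguard, and the comparison of standards can be biased.

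A reader might go further and conclude that the design biases the comparison against LAO. The article does not support that. Unequal numbers alone do not bias a mean. The direction against LAO needs best-case choice in both techniques, recording pools of similar size (or a larger OO pool), and LAO scores that are averaged or judged on the worse video. None of these is fixed. The article's remarks on recording make a smaller OO pool plausible, which could turn the sign.

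The size is about −0.2 to −0.6 SD for LAO with equal pools of 2 to 50 and averaged scores, and +0.83 to +1.27 SD with one OO recording and LAO chosen from 5 or 10. These figures rest on the assumptions of equal skill, normal independent scores and free choice, not on data in the article. The failure to prevent selection does not depend on the figures, since it follows from the absence of a selection rule.

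**What to change.** Use one selection rule for both techniques. Videos come from the next consecutive consenting case(s) after the surgeon registers, and the case is logged before the operation starts. Keep an incomplete video on file and replace it with the next consecutive case. When techniques are compared, report poor judgements per video and not per surgeon. Unless the consecutive-case rule is adopted, change the claim that two videos prevent best-case selection to a claim that they reduce it.

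Equal numbers per technique are not needed to remove the bias once cases are consecutive, so the second LAO video can stay and no data need be discarded.

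The cost is a case log and a paragraph in the planned video operating procedure. A surgeon may have to wait for the next consenting case, and some videos will show harder operations.

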**Figure 2 F2:**
[figure not shown]
Schema for the development of a pretrial QA tool to assess surgeons’ overall operative technique in relation to oesophagectomy. HTA-O, Hierarchical Task Analysis for Oesophagectomy 8; OSATS, Objective Structured Assessment of Technical Skills; QA, quality assurance; ROMIO, Randomised Oesophagectomy–Minimally Invasive or Open.^9^

